# Impact of medication review via tele-expertise on unplanned hospitalizations at 3 months of nursing homes patients (TEM-EHPAD): study protocol for a randomized controlled trial

**DOI:** 10.1186/s12877-020-01546-3

**Published:** 2020-04-20

**Keywords:** Drug, Elderly, Iatrogenic, Inappropriate medication, Telemedicine, Tele-expertise

## Abstract

**Background:**

Inappropriate drug prescribing causes preventable drug-related adverse events that result in increased morbidity and mortality, additional costs and diminished quality of life. Numerous initiatives have been launched to improve the quality of drug prescribing and safeguard the security of drug administration processes in nursing homes. Against the backdrop of implementation of telemedicine services, the focus of the present work is to evaluate the impact of a telemedication review carried out by a hospital physician and pharmacist as part of the telemedicine offer.

**Methods:**

The present study is a randomized controlled clinical trial. A total of 364 patients will be randomized into two groups: (1) an experimental group (182 patients) benefiting from a telemedication review using tele-expertise and (2) a control group (182 patients) receiving standard care. The primary endpoint will be rate of all-cause unplanned hospital admissions occurring within 3 months of randomization. The secondary endpoints will be rate of unplanned admissions at 6 months, patient quality of life, incidence of behavioral disturbances, number of falls, number of residents prescribed at least one inappropriate medication, nursing staff satisfaction, proposed medication reviews and their acceptability rate, characteristics of patients whose general practitioners have taken account of tele-expertise, efficacy of tele-expertise as compared to standard prescription and acceptability and satisfaction surveys of participating caregivers.

**Discussion:**

In the literature, various studies have investigated the utility of structured medication review processes, but outcome measures are heterogeneous, and results vary widely. Medication review can detect medication-related problems in many patients, but evidence of clinical impact is scant. Incremental cost-effectiveness ratios will be used to compare the cost and effectiveness of the experimental strategy and that of standard care. Our approach, involving the combination of an acceptability survey and a mixed-method (qualitative and quantitative) satisfaction survey, is particularly innovative. The results of this randomized trial are expected to confirm that medication review using tele-expertise has potential as a worthwhile care management strategy for nursing home residents.

**Trial registration:**

Clinicaltrials.gov NCT03640845; registered August 21, 2018 (Clinicaltrials.gov NCT03640845).

## Contributions to the literature

Our paper will determine the impact of telemedication review at high iatrogenic risk on unplanned hospital admission in addition to health-related quality of life, behavioral disturbances, frequency of falls, potentially inappropriate medications and convenience of drug administration for nursing staffWe will provide insight into the impact of tele-expertise in terms of health economics with a cost effectiveness study.Ultimately, we will attempt to determine which organizational and psychosocial factors are likely to facilitate or on the contrary to hamper telemedication review development and acceptability

## Background

One of the effects of population aging is increasing the risk of drug-induced iatrogenic disease for whom appropriate prescription is not just a matter of healthcare quality and safety but also one of its economic efficiency [1]. The challenge for the prescriber when treating older multimorbid patients is to strike a balance between optimizing chronic disease control and minimizing the risks of polypharmacy. In the elderly population, potentially inappropriate medication use, drug–drug interaction or drug–disease interaction are associated with negative health outcomes and contribute significantly to 6–17% of hospital admissions in older adults [2–5]. In France, medication-induced iatrogenic disease is believed to account for over 10% of hospital admissions in patients over 65 years of age, 20% of admissions in patients over 75 years of age and 25% of admissions in those over the age of 85 [6]. Given that 30 to 60% of adverse drug events are thought to be foreseeable and avoidable, improving the quality and safety of drug prescription is of paramount importance for public health, particularly in elderly patients [7].

In nursing homes, residents accumulate a mean of 8 comorbidities (85% of residents present neuropsychiatric disorders and 75% cardiovascular disease), take a mean of 8 different medications per day and roughly one third of them suffer from swallowing disorders [8, 9]. According to data analysis from an experimental project to re-establish medication as part of care plans offered by nursing homes with no in-house pharmacy in the Aquitaine and Limousin regions of France in 2012, 25% of residents were subjected to excessive treatment and 70% were found to have been prescribed medication unnecessarily. It is also necessary to add the omission of potentially appropriate medication (i.e. no drug prescription despite indication). Other factors also promote medication-induced iatrogenic disease in elderly patients, such as pharmacodynamic and pharmacokinetic alterations as well as multiple prescribers. Systematic review shows that almost one half of nursing home residents are exposed to potentially inappropriate medications and suggests an increase prevalence over time [10]. Effective interventions are therefore required to optimize drug prescribing in nursing home facilities.

Several recommendations aimed at addressing these concerns have been issued on a national scale [11–13]. Numerous initiatives have also been launched to improve the quality of drug prescribing and the security of drug administration processes in nursing homes, and these initiatives are supported by various nationwide schemes. Systematic medication review is a simple and effective way of minimizing inappropriate drug prescription and optimizing how medication is prescribed to this population [14, 15]. Within the framework of this approach, it is essential to obtain an accurate insight into a patient’s treatment with regard to the comorbidities and potential geriatric syndromes involved, the patient’s wishes and any available pharmacological evaluation tools, such as STOPP/START.v2 criteria or the Laroche list. Medication review in older adults must also be conducted in accordance with healthcare objectives centered primarily on patients and their independence; this is particularly applicable to patients who are frail, suffering from multiple comorbidities and/or very elderly. The suitability of each medication should be discussed in terms of expected benefits and risk of adverse events while also taking into consideration patient preference and life expectancy. The main purpose of this type of review is to optimize drug prescription and ensure that more good is done than harm.

Nowadays telemedicine embodies a new way of structuring medical practice. It is a potential vehicle for better access to healthcare since it overcomes patient transport difficulties and mitigates the chances of a patient refusing healthcare (for geographical, economic or social reasons), thereby improving quality of care (in terms of avoidable hospital admission and reduced utilization of emergency services) and minimizing use of healthcare resources (such as healthcare consumption and transport costs) [16]. Tele-expertise (TE) allows a doctor, dubbed the “requesting” physician, to ask advice on the strength of specialist training or skills from a colleague, dubbed the “consulting” physician, based on details or elements from a patient’s medical records, without the patient’s physical presence. Until the end of 2020, TE in France will only apply to patients requiring help with access to healthcare on account of their state of health or geographical circumstances; residents from nursing homes fall into this category. Accounts of telemedicine found in the literature essentially focus on TE (recommendations on findings from follow-up examinations related to dermatological problems or chronic wounds for example) and telemonitoring for chronic disease such as heart failure [17–20]. To our knowledge, there are no telemedication review (TMR) in the literature. The purpose of the present study is to evaluate the impact of TMR regarding residents at high iatrogenic risk versus standard care on unplanned hospital admission rates at 3 and 6 months in addition to health-related quality of life, behavioral disturbances, frequency of falls, potentially inappropriate medications and convenience of drug administration for nursing staff. This study will also provide an assessment of the impact of TE in terms of health economics. Finally, a qualitative study conducted by the regional health observatory will contribute to a better understanding of the organizational and psychosocial factors associated with the success of this approach or conversely those that have hampered its acceptability and its development.

## Methods

### Study design

This prospective, multicenter, single-blind, randomized, parallel-group trial is conducted in accordance with the ethical principles of the Declaration of Helsinki and the principles of current Good Clinical Practices. The study protocol (Version 2, 29/10/2019) is designed in accordance with guidelines from the Consolidated Standard of Reporting Trials (CONSORT) statement.

### Recruitment and randomization

Recruitment will take place within consenting nursing homes contacted by the gerontology coordination groups of Marseille. Nursing home coordinating physicians will act as study investigators in charge of patient inclusion. Written consent to participate will be obtained at the Nursing home after the investigator has provided all necessary information about the study. Randomization will be performed at patient level, with eligible patients randomly assigned in a 1:1 ratio to the control group (non-intervention) or the experimental group (TMR) based on a computer-generated permuted-block randomization schedule with blocks of four. Randomization is to be stratified by an adverse drug event risk detection score in elderly patients, the Trivalle’s risk score (≤ 5 or > 5). Based on the IMEPAG study [21], this score is both easy and practical to use for detecting the risk of adverse drug events in elderly patients. Risk factors included in the score are: number of medications (if greater than or equal to 7), antipsychotic treatment and recent anticoagulant treatment (dating back less than 3 months). Each parameter is scored on a scale from 0 to 10, with 0–1 corresponding to an adverse drug event risk of 12%, 2–5 corresponding to a 32% risk and 6–10 to a 53% risk.

Computer-generated randomized lists will be drawn up before the beginning of the study under the responsibility of the local Clinical Research Unit. Methodological support will be provided by the Clinical Research Unit. Study investigators will not be blinded to group allocation. The recruitment period will span 20 months, and patient follow-up will last 6 months (Table 1).

**Table 1 Tab1:** Timeline of the study

Timepoint	Study Period			
	Enrolment	Inital assessment	Follow-up at 3 months	Follow-up at 6 months

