## Discussion

On account of iatrogenic disease that may stem from the utilization of prescribed medication and the resulting negative consequences for health in the elderly, better prescribing in this population has been recognized by the World Health Organization (WHO) in its recent report on aging and health as a high-priority area of focus [35]. Medication optimization in these patients can nevertheless prove to be challenging since there is a dearth of evidence-based medical data pertaining to the implementation of therapeutic guidelines in frail or even physically dependent elderly patients with multiple comorbidities and polypharmacy. A 2013 report by P. Verger on medication policy in nursing homes confirms that it is vital to promote regular medication review [36]. Medication optimization is a valuable means of checking whether each medication is still indicated for and of clinical benefit to the condition under consideration, of checking possible contraindications whether dosage is optimal, of questioning whether dosage form is appropriate (i.e. in the event of swallowing disorders) and whether a patient self-medicates. It also provides an overview of current medical conditions and highlights those requiring prompt treatment. Nursing home patients are an important target population for medication optimization in the elderly. Transport difficulties and time constraints on GP impede review of and improvements to drug prescribing. Indeed, healthcare professionals broadly observed that GP invest little time in medication management within nursing homes. With this in mind, the interest to offer a personalized medication review in nursing homes remain. In the literature, various studies have investigated the utility of structured medication review processes, but outcome measures are heterogeneous, and results vary widely. Medication review can detect medication-related problems in many patients, but evidence of clinical impact is scant. There is little evidence that medication reconciliation and medication review processes, as currently performed, significantly improve clinical outcomes [37]. The only significant change observed was a reduction in falls while no changes in mortality, resident behavior, hospital admission rates, functional status or cognitive skills have been noted so far [38–40]. We have therefore decided to evaluate the impact of TMR of nursing home patients on unplanned hospital admissions and other criteria, as assessed by a hospital team within the context of a randomized controlled study. This is a growing research field and fortunately similar studies are under way. The InTherAKT study is a single-arm study whose aim is to optimize communication between the healthcare professionals involved by specific training and by establishing a structured medication review process, and to improve medication appropriateness in line with the Medication Appropriateness Index for nursing home residents [41]. The HIOPP-3-iTBX study investigates the effects of pharmacist-led medication reviews linked with measures to strengthen interprofessional cooperation with regard to the quality of medication, health status and health care use of nursing home residents in a cluster randomized controlled trial [42]. The SCREAM study is a randomized study aimed at implementing a computerized clinical decision support system that analyzes nursing home resident medications in terms of interactions, appropriateness of dosage and other clinical data to minimize the time resources required for medication reviews by pharmacists and nursing home physicians [43]. On account of the mobility problems encountered by nursing home residents and the limited resources at the disposal of mobile geriatric care units to reach the various institutions, we have decided to intervene via telehealth program. Telemedicine is an alternative means of delivering care that calls for the same quality and safety standards as conventional healthcare. By analyzing all of the criteria involved in medication management (medication reconciliation, clinical and biological parameters, previous history etc.), telemedicine provides specific expert recommendations both remotely but also as closely as possible to where patients live. It is also instrumental in improving the efficiency and logistics of healthcare. Its goal is not to replace face-to-face medical treatment but to complement conventional healthcare. Rather than taking the place of customary medical practice, it constitutes a means of overcoming the challenges facing present-day healthcare provision. In our study, management decision-making lies firmly with the GP who is at liberty to accept or refuse the recommendations put forward. Thus, there is a risk of zero impact if GP refuse to at least partially take on board recommendations arising from TMR. Hence, we feel it is important to investigate how this intervention is perceived and received and to ascertain potential organizational and psychosocial factors prone to facilitate or on the contrary hamper its implementation, acceptability and impact on patients. The combination of both an acceptability survey and a satisfaction survey, the latter of which uses a mixed-method (qualitative and quantitative) approach, is particularly innovative. Indeed, in similar previous projects, feasibility/experience assessment was conducted using qualitative or quantitative methods alone [44, 45], or focused solely on post-intervention evaluation [46, 47]. Moreover, the WHO defines “acceptability to participants” as an essential ethical issue in study design [48]. Owing to the economic issues at stake in this new type of practice, we will also evaluate the impact in terms of cost-effectiveness of TMR as compared to standard healthcare. The benefits of collaboration between geriatric physicians and clinical pharmacists have already been borne out by other research teams [49, 50]. The feasibility of the proposed study relies on hospital teams that are already familiar with reconciliation and have received training in geriatric medication review. The number of nursing homes agreeing to participate means that only 20% of the residents will be required for inclusion, which appears perfectly feasible according to presentation of the present study to the coordinating physicians who will be in charge of inclusion. Moreover, additional nursing homes have expressed their desire to participate since the start of the study, making a total of 17 nursing homes. Financial compensation for each inclusion will be paid to coordinating physicians and, bearing in mind that TMR may mean that GP will need to take time to adjust their prescriptions, they too will receive payment equivalent to a home visit for each patient included in the experimental group. Data collection will be conducted by clinical research assistants to minimize any risks of missing data that may have occurred had we overburdened the coordinating physicians.

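### A constant block size of four, published while unblinded physicians were still choosing whom to include, creates an avoidable risk of predictable allocation if homes enrol residents in runs

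*Protocol article*

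**What the plan says.** All of the following is from the protocol article.

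- **Schedule.** Recruitment and randomization specifies individual 1:1 allocation from a "computer-generated permuted-block randomization schedule with blocks of four". The only stratum named is the Trivalle score, at or below 5 versus above 5. Nursing home is not a stratum.
- **Lists.** "Computer-generated randomized lists will be drawn up before the beginning of the study under the responsibility of the local Clinical Research Unit".
- **Recruiters.** "Nursing home coordinating physicians will act as study investigators in charge of patient inclusion", and "Study investigators will not be blinded to group allocation".
- **Room for choice.** The Discussion expects to need only 20% of the residents of the participating homes and describes late joiners "making a total of 17 nursing homes".
- **Timing.** Enrolment began in April 2019 and was planned to last 20 months. The trial was recruiting in March 2020, and the article is dated 20 April 2020.
- **Primary analysis.** An unadjusted chi-square or Fisher's exact test of the 3-month unplanned admission rate. Covariate-adjusted logistic regression and a mixed model with center as a random effect are secondary.

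**The concern.** In a permuted block of known size, past allocations carry information about the next one. Here the size does not vary, it was made public about 12 months into a 20-month recruitment, and the person who picks the next resident is not blinded to allocation. The Trivalle score is recorded at enrolment, so the recruiter also knows which list the next resident will draw from.

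A physician who can guess the next arm better than by chance can, deliberately or not, choose which eligible resident to approach next. The arms could then differ in baseline admission risk. Masking the outcome assessment would not correct this, and the unadjusted primary test would not remove it. The secondary regression could adjust only for risk differences that are measured.

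**Working it through.** The article gives no figure for predictability, so there is none to reproduce.

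**Inputs from the article:** block size 4, ratio 1:1, two strata, 17 homes, 364 patients. That is 364/17 = 21.4 residents per home and 364/20/17 = 1.1 per home per month. **Assumptions, not in the article:** the length of runs within a home, whether the recruiter knows where a block starts, and the share of residents in the higher-risk stratum (20 to 50% used).

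**1. Fixed blocks of four, all allocations seen, block start known.**

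- Certain allocations: with probability 1/3 the first two are alike and the last two are then certain. With probability 2/3 they differ and only the last is certain. (1/3)(2) + (2/3)(1) = 4/3 per block, and (4/3)/4 = 33.3%.
- Best-guess accuracy by position: 1/2, 2/3, 2/3, 1. The sum is 2.833, and 2.833/4 = 70.8%.

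**2. Block start unknown.** Take the four possible starting positions as equally likely and update after each allocation. For a run of two, the second differs from the first with probability (3/4)(2/3) + (1/4)(1/2) = 0.625, so accuracy is (0.5 + 0.625)/2 = 56.2%. Longer runs were enumerated exactly in the same way.

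**3. Fixed fours against blocks of 4, 6 or 8 drawn with equal probability.** The guesser is assumed to know the set of sizes but not which one is in use. The run is consecutive, in one stratum and one home.

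| Run | Block start | Best guess, fixed 4 | Best guess, 4/6/8 | Certain, fixed 4 | Certain, 4/6/8 |
|---|---|---|---|---|---|
| 2 | unknown | 56.2% | 54.2% | 0% | 0% |
| 4 | unknown | 61.1% | 57.3% | 0% | 0% |
| 8 | unknown | 65.5% | 60.8% | 3.6% | 0% |
| 4 | known | 70.8% | 62.5% | 33.3% | 0% |
| 8 | known | 70.8% | 66.2% | 33.3% | 2.9% |

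**4. Two lists shared by 17 homes.** In a simulation of 364 patients, each physician sees only the allocations in the home, block starts are known, and runs are of residents of either stratum:

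| Enrolment pattern | Certain | Best guess |
|---|---|---|
| Fully interleaved | about 0.1% | 51% |
| Runs of 4 per home | 5 to 8% | 58 to 59% |
| Runs of 8 per home | 15 to 18% | 62 to 64% |
| Runs of 21 per home | about 26% | 67 to 68% |

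**5. What this could do to the comparison.** Suppose a recruiter steers higher-risk residents to one arm and lower-risk residents to the other, with a risk gap d between them and guess accuracy g. The spurious difference between arms is g·d − (1 − g)·d = (2g − 1)d. At g = 0.51 this is 0.02d, at 0.655 it is 0.31d, at 0.608 it is 0.22d, and at 0.708 it is 0.42d. The article gives no basis for d. The expression assumes steering at every inclusion, so it is an upper bound for a given d and g.

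**The case against.** The strongest objection is that the lists appear to be shared. With 17 homes drawing on two lists and about 1.1 inclusions per home per month, one physician would usually see only fragments of a block. Under full interleaving the advantage is negligible. This stands, and it is why the point is conditional. The article does not say how enrolment is ordered. Homes of about 21 participants each, some joining after the start, make runs plausible but do not establish them.

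A reader might infer that one third of allocations are predictable. That needs a recruiter who sees every allocation in a block and knows where the block begins on a list used by 16 other homes. The article supports neither. With the start unknown, a run of eight gives 3.6% certain.

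A reader might also see a motive in the sentence "Financial compensation for each inclusion will be paid to coordinating physicians". That payment does not depend on the arm. The payment that does depend on the arm goes to general practitioners, who do not recruit. No passage gives recruiters a reason to prefer one arm, and none shows that steering occurred.

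Three further limits stand:

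- Residents who all consent before any of them is allocated cannot be selected on a guess; only their order could be manipulated.
- How allocations are released may be described in the full protocol and is no finding here. Central release would still not prevent inference from past allocations and a known block size.
- Varying the block size is not better on every measure. For a run of eight with known start, the share of allocations guessable with at least 70% certainty rises from 33% to 49%, although certain allocations and overall accuracy both fall.

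**Conclusion.** The point holds as a conditional and avoidable risk. The article states a constant block size, its publication during recruitment, and unblinded recruiters with wide choice of residents. That these recruiters learn the allocations in their own home is a close inference from the lack of blinding. Guessing accuracy then ranges from 51%, if homes interleave, to about 66% (start unknown) or 71% (start known) for eight consecutive residents of one stratum in one home. The article does not settle where in this range the trial lies. It does not support saying that allocations are predictable or that the trial is biased. It does support saying that the design leaves open a route to selection bias that the primary test would not correct and that is cheap to narrow.

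**What to change.** The Clinical Research Unit should regenerate the unused part of both Trivalle-stratum lists with randomly varying block sizes, for example 4, 6 and 8. The sizes should be neither disclosed to the homes nor published until recruitment closes. The 1:1 ratio and the stratification stay as they are.

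Across the clustered scenarios in the first table, this lowers best-guess accuracy by about 2 to 8 percentage points. For a run of eight it also reduces certain allocations from 3.6% to 0% (start unknown) or from 33% to about 3% (start known).

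The cost is a protocol amendment, two new lists, and a maximum arm imbalance of 4 instead of 2 per stratum. Sample size and planned power do not change.
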